#### Sample size

The sample size calculation was performed using the PASS15 software, Version 15.0.5, with reference to a prior randomized controlled trial conducted in China that reported the Wexner score as the primary outcome [27]. We selected a significance level of 0.05 and a power of 90%. Assumptions encompassed an equal allocation of participants in a 1:1 ratio between two groups and a 20% dropout rate. The mean for group 1 (μ_1_) was 10.65, and group 2 (μ_2_) was 9.10. The standard deviation for group 1 (σ_1_) was 2.08, and for group 2 (σ2), it was 1.73. The anticipated effect size was 0.81. The sample size calculation indicated that each group should comprise 40 patients.

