### Data collection and management

Demographic and baseline information will be collected during the initial assessment. Participants will complete a well-designed questionnaire that encompasses age, sex, height, weight, types of strokes, and medication usage. The data collection will be conducted by a staff member who is not involved in the study. Data will be collected at five time points: during screening, baseline, at post-2-week intervention, at post-6-week intervention, and at 12-week follow-up. The comprehensive data collection plan is presented in Table 1. To ensure confidentiality, each participant will be assigned a unique identifier, and all collected information will be securely stored in an electronic file. Data access will be restricted until statisticians complete the data analysis at the conclusion of the study. After a period of 3 years, all data will be deleted.

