### Statistical analyses

The collected data will undergo analysis using IBM SPSS Statistics 25.0 (IBM Corp., Armonk, NY, USA). Baseline characteristics will be summarized using descriptive statistics. Continuous variables, such as the Wexner score and quality of life score, will be reported using means, medians, standard deviations, and score ranges. Categorical valuable, such as BSFS, will be reported as counts and percentages. To ascertain normality, the Kolmogorov-Smirnova test will be applied. In instances of normally distributed data, independent samples *t*-test will be employed to compare efficacy between the intervention and control groups in terms of the Wexner score, PAC-QoL, and FI-QoL. Non-normally distributed data will be analyzed using the Wilcoxon rank sum test with a test statistic of *Z*. For assessing changes across distinct time points, we will employ repeated measures ANOVA. The chi-squared test will be used to analyze categorical data for the BSFS. A *p*-value < 0.05 will be considered statistically significant. We will perform an intention to treat analysis for participants who either lack adherence to bowel care (defined as comply with less than 80% of bowel care) or discontinue the study. These participants will be retained within their originally randomized treatment arm for analysis. Addressing missing data, a multiple imputation method will be implemented. No supplementary analyses will be carried out in this study, and the study design does not encompass interim analyses.

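### The normality-gated unadjusted tests and separate repeated-measures ANOVA sit awkwardly with multiple imputation and leave baseline score and NIHSS stratum unused; one mixed model would serve better

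*Protocol article*

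**What the plan says.** The Statistical analyses section of the protocol article fixes these elements:

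- A Kolmogorov-Smirnov test decides normality.
- If the data pass: "In instances of normally distributed data, independent samples *t*-test will be employed to compare efficacy between the intervention and control groups", for Wexner, PAC-QoL and FI-QoL.
- If they fail: "Non-normally distributed data will be analyzed using the Wilcoxon rank sum test", with Z as the statistic.
- Over time: "For assessing changes across distinct time points, we will employ repeated measures ANOVA". No link to the normality decision is given.
- For stool form: "The chi-squared test will be used to analyze categorical data for the BSFS".
- For missing values: "Addressing missing data, a multiple imputation method will be implemented".

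Participants who discontinue stay in their randomized arm, and supplementary analyses are ruled out. The Sample size section assumes "a 20% dropout rate". Data collection and management lists screening and baseline, then assessments "at post-2-week intervention, at post-6-week intervention, and at 12-week follow-up". Randomization is stratified by baseline NIHSS (0–4 and 5–15), according to Allocation—sequence generation. None of the named between-arm tests uses that stratum or the baseline score.

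**The concern.** Multiple imputation produces several completed data sets. The basic form of Rubin's rules turns them into one result by combining an estimate and its standard error. Of the four named tests, only the t-test supplies that pair directly. A rank-sum Z, an ANOVA F and a chi-squared statistic need a different combining rule. The normality gate adds a complication: if it is applied within each completed data set, it can send the same outcome to a t-test in one set and a rank-sum test in another.

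Two features would be weak even with no missing data. First, the between-arm tests are unadjusted, although baseline score and NIHSS stratum are already collected and the stratum is used for randomization. Second, the ANOVA relies on sphericity across unequally spaced visits and stays in place when the same scores have been judged non-normal. At stake are precision in a trial of 80 participants and an estimate with a confidence interval that follows clearly from the stated method.

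**Working it through.** **Inputs.** From Sample size: means 10.65 and 9.10, SDs 2.08 and 1.73, alpha 0.05 (two-sided assumed), power 90%, dropout 20%, 40 per group. From Data collection and management: baseline and weeks 2, 6 and 12 (taken as weeks from baseline). Assumed, because the article does not give them: normal scores, values missing completely at random, between-visit correlations, and number of imputations M.

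**1. The plan's own figure.** Root-mean-square SD = √[(2.08² + 1.73²)/2] = 1.913. Effect = 1.55/1.913 = 0.81, as stated. n = 2(1.960 + 1.282)²/0.81² = 32.01, so 33 per arm. 33 × 1.2 = 39.6, which rounds up to the stated 40 (33/0.8 gives 42). The figure reproduces and does not affect this point. It implies 20% × 40 = 8 missing and 32 observed per arm.

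**2. Can the rank-sum result be pooled?** Rubin's rules use the mean estimate and T = Ū + (1 + 1/M)B, where Ū is the mean within-set variance and B the between-set variance. For a statistic w on k degrees of freedom, the D2 rule uses r = (1 + 1/M) × var(√w) and D2 = [w̄/k − r(M + 1)/(M − 1)]/(1 + r), referred to an F distribution. Simulation: 2,000 trials, 40 per arm, 8 missing per arm, M = 20, baseline correlation 0.5.

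| Pooled method | Rejection, no effect | Rejection, 0.81 SD |
|---|---|---|
| t-test mean difference, Rubin | 5.0% | 90.8% |
| Rank-sum Z squared, D2 | 5.2% | 88.9% |
| Mann-Whitney probability, Rubin | 5.5% | 89.6% |

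The Monte Carlo standard error at 5% is √(0.05 × 0.95/2000) = 0.5 percentage points, so all three agree with 5%.

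**3. What if nothing is pooled?** Share of trials in which the per-set rank-sum p-values fall on both sides of 0.05:

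| | No effect | 0.5 SD | 0.81 SD |
|---|---|---|---|
| M = 5, correlation 0.3–0.6 | 13–17% | 32–36% | 14–17% |
| M = 20, correlation 0.5 | 28% | not run | 26% |

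**4. What does ignoring baseline cost?** Adjusting for a baseline with correlation ρ shrinks the residual SD by √(1 − ρ²), so the effect becomes d/√(1 − ρ²). With 32 per arm the noncentrality is d√(32/2) = 4d.

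| d | Unadjusted | ρ = 0.3 | ρ = 0.6 |
|---|---|---|---|
| 0.5 | 4 × 0.5 = 2.00, power 50% | 4 × 0.524 = 2.10, 54% | 4 × 0.625 = 2.50, 69% |
| 0.81 | 4 × 0.81 = 3.24, power 89% | 4 × 0.849 = 3.40, 92% | 4 × 1.0125 = 4.05, 98% |

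Simulation with 40 per arm and 20% missing gives the same picture at 0.5 SD: 46–56% unadjusted and 50–72% baseline-adjusted, with type I error at or below 5%. The further gain from the NIHSS stratum was not quantified.

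**5. Sphericity.** Take correlation a^(gap in weeks/2) with a = 0.85 to 0.95. For a = 0.85, baseline correlates 0.85, 0.61 and 0.38 with weeks 2, 6 and 12. With A = C′ΣC for orthonormal contrasts C, Greenhouse-Geisser ε = (tr A)²/[3 tr(A²)], which gives 0.70 at a = 0.85 and 0.63 at a = 0.95. In 20,000 null trials with 32 per arm, the uncorrected group-by-time F rejects in 6.8–7.4%. The same formula at equally spaced weeks 0, 4, 8 and 12 gives ε of 0.76 to 0.68. The decay is therefore the main cause and the unequal spacing adds to it. Under equal correlations ε = 1 and there is no inflation.

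**The case against.** The strongest reply is that the article contains no error here, only condensation. The number of imputations, the imputation model, the combining rule, any sphericity correction, and whether normality is checked once or per set are details that an article commonly leaves to the full protocol or analysis plan. That stands, and their absence is not held against the plan. It is also true that the t-test route for the primary outcome pools directly.

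Three stronger readings are tempting, and the documents support none of them:

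- **That the plan cannot give one valid result per outcome.** The Z, F and chi-squared statistics can be combined by D2-type rules, and the table above shows the rank-sum version holding its level. Nowhere does the article say that per-set p-values will be reported or used.
- **That false positives rise to 7–12%.** Rates of 7–10% arise if one imputed set is tested, and 8–12% if the imputations are averaged before testing. The article proposes neither.
- **That the ANOVA has only 56–65% power.** This describes its group main effect with baseline counted as a time level. The article assigns the ANOVA to change over time, gives the efficacy comparison to the t-test or rank-sum test, and does not say that baseline is a level.

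It may also be said that a mixed model is a preference, since multiple imputation is accepted under the same missing-at-random assumption. That is fair as far as missing data go. It does not answer the unused baseline score and stratum, or the ANOVA's separation from the normality gate. Those follow from methods that the article itself fixes.

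**Conclusion.** The concern holds as an advisable improvement to the analysis method. It does not show that the plan is invalid. Conflicting p-values across imputed sets are possible but not inevitable, and a pooling rule removes them.

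What survives is the choice of tests. Leaving out the baseline score costs about 4 to 19 points of power at an assumed 0.5 SD (50% against 54–69%), and about 3 to 9 points at the design effect of 0.81 SD (89% against 92–98%), for assumed correlations of 0.3 to 0.6. The type I error of about 7% applies only to an uncorrected ANOVA under time-decaying correlation. These sizes rest on normal data, 8 missing per arm completely at random, and correlations that the article does not report. The 20% dropout is a planning figure, not observed missingness.

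**What to change.** For Wexner, PAC-QoL and FI-QoL, replace the gated t-test or rank-sum test and the repeated-measures ANOVA with one linear mixed model for repeated measures:

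- Outcomes: the post-baseline visits, using all observed data.
- Terms: arm, visit, arm-by-visit, baseline score and NIHSS stratum.
- Covariance: unstructured, which removes the sphericity assumption.
- Report: the arm difference with its 95% confidence interval at the designated visit.

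Under missing-at-random this needs no imputation of the post-baseline scores. Where imputation is kept, for example for BSFS, either pool an estimate with its standard error (such as a logistic regression coefficient for stool types III–IV versus other types) or state that the chi-squared statistic will be pooled by a D2 rule.

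The cost is analysis wording only: no new data are needed, and the model is available in the named software family. The small downside is a model-based result in place of simple tests.

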### Plans to give access to the full protocol, participant-level data

We will deliver a fully deidentified data set to an appropriate data archive no later than 3 years after the completion of data collection.

### Composition of the coordinating center

The coordinating center team, established at the First Hospital of Changsha, will comprise a multidisciplinary team consisting of a director of nursing, two directors of rehabilitation medicine, and five graduate students. This coordinating center will be tasked roles, including overseeing subject recruitment, personnel management, and implementation hospital-based interventions. The trial steering committee, constituted by members from the School of Nursing, University of South China, will feature seasoned researchers and clinical specialists. The committee members will be responsible for subject recruitment produces, regular monitoring activities, and data verification at the conclusion of the trial.

### Composition and responsibilities of the data monitoring committee

In line with commitment to participant safety and the reliability of research outcomes, an independent data monitoring committee will be instituted. This committee will oversee trial data and adverse reactions as well as provide insightful suggestions. Monthly meetings will be convened to deliberate on trial progress, safety parameters, and data quality. Additionally, meetings will be scheduled in response to any concerns related to participant safety.

### Adverse events and harms

This study identifies adverse events encompassing abdominal pain, anal fissure, and anal bleeding. Rigorous collection of all adverse events, as well as any unexpected reactions, will be executed through both subject self-reports and investigator observations. A standardized classification system in accordance with the Common Terminology Criteria for Adverse Events (CTCAE) will be employed. We will report adverse events categorized as level 2 or higher to the DMC within 24 h. The reporting will include details on severity, occurrence time, duration, actions taken, outcomes, and causality assessment. The follow-up for adverse events will span a period of 12 months post-intervention.

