## Interventions

### Control group

The participants in the control group will be receive standard care, consisting of dietary guidance, pelvic floor muscle exercises, and skin care. In the event of no enhancement in bowel function over a span of 3 days, prescribed enemas or appropriate medications will be administered as needed.

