### Experimental group

Participants in the intervention group will receive an additional intervention that includes DRS and abdominal massage, in addition to the standard care.

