### Digital rectal stimulation

The procedure of DRS involves gently inserting either the middle or index finger into the anus. The rectal wall is then gently stimulated in a clockwise direction, creating a circular motion. After completing ten circles, there is a brief pause for 1–2 min. The duration of stimulation is adjusted based on various factors, including the patient’s rectal content, stool consistency, and sphincter muscle strength. The stimulation duration is set at 8 min for mild sphincter injury (anal systolic pressure 15–25 mmHg), 10 min for moderate to severe sphincter injury (anal systolic pressure 0–15 mmHg), and 15 min for severe sphincter injury (anal systolic pressure 0 mmHg). If the patient’s rectal fecal volume exceeds 100 g, the stimulation time is extended accordingly.

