## Assignment of interventions: blinding

### Who will be blinded

A third party will oversee the management and coding all data, maintaining the confidentiality of codes until the data analysis is completed. The data analyst will be blinded to the codes. The evaluation of outcomes will be performed by an assessor who is unaware to treatment allocation and has undergone training. However, it is important to note that due to the nature of bowel rehabilitation program, neither implementers of intervention nor participants can be blinded to the intervention.

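### Adverse event collection is not stated to be blinded or equal between arms, so the comparison of anal bleeding, anal fissure and abdominal pain is at risk of detection bias

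*Protocol article*

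**What the plan says.** **How harms are collected.** Under Adverse events and harms, the article names the events of interest: "This study identifies adverse events encompassing abdominal pain, anal fissure, and anal bleeding". Collection of these and of any unexpected reactions "will be executed through both subject self-reports and investigator observations". Events are classified by CTCAE. Those of level 2 or higher go to the data monitoring committee within 24 hours, with details that include timing and causality. The section does not say who observes, grades or assigns causality, whether that person knows the allocation, or whether both arms are questioned alike.

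**Who is blinded.** Under Who will be blinded, "neither implementers of intervention nor participants can be blinded to the intervention". A blinded role does exist: "The evaluation of outcomes will be performed by an assessor who is unaware to treatment allocation and has undergone training". The article does not extend that role to adverse events.

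**Contact by arm.** Under Experimental group, "Participants in the intervention group will receive an additional intervention that includes DRS and abdominal massage, in addition to the standard care". Under Digital rectal stimulation, "The procedure of DRS involves gently inserting either the middle or index finger into the anus". Control care is described as "consisting of dietary guidance, pelvic floor muscle exercises, and skin care", with enemas or medication if there is no improvement over 3 days.

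**Why harms matter here.** The abstract makes safety a study aim alongside effectiveness. The hypothesis at the end of the Background expects superiority with few complications.

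**The concern.** All three named events arise where the intervention is applied: two at the anus and one in the abdomen. Someone giving DRS or massage is well placed to notice bleeding, a lesion or pain, or to be told of it. A control participant has no planned contact of that kind. Participants in both arms know their allocation, so the self-report half of the method is open to differential reporting whoever the investigators are.

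If detection differs by arm, the difference in adverse event counts mixes true harm with intensity of surveillance. With 40 patients per group, counts are likely to be small, and one or two events seen in one arm but missed in the other could change how the safety result reads. The absence of a formal test does not remove the problem, because a descriptive table is distorted in the same way.

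**Working it through.** **Step 1: the document's own figures.** The article gives no adverse event rate and no detection probability, so there is no stated harm figure to reproduce. The only figure used below is the planned 40 per group, from Sample size.

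**Step 2: the text, side by side.**

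| Feature | Intervention arm | Control arm |
|---|---|---|
| Participant blinded | No | No |
| Planned digital rectal contact | Yes | No |
| Planned abdominal massage | Yes | No |
| Enemas as needed; perineal cleaning in fecal incontinence | Yes (standard care) | Yes (standard care) |
| Diary and on-site observations | Yes | Yes (no arm restriction stated) |
| Common adverse event questions or inspection schedule | Not stated | Not stated |

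The DRS section gives no session frequency. That contact is repeated follows from the 6-week programme and from adherence being defined as a percentage of bowel care.

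**Step 3: what unequal detection would do (every rate here is assumed).** Let p be the true event rate and s the probability that an event is recorded. Then

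- observed rate = p × s
- observed risk ratio = true risk ratio × (s under intervention ÷ s under control)

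Take equal true rates (true ratio 1.00) and 90% detection under intervention. For p = 10%:

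| Detection under control | Observed rates | Observed ratio | Expected events among 40 per arm |
|---|---|---|---|
| 90% | 9% vs 9% | 1.00 | 3.6 vs 3.6 |
| 70% | 9% vs 7% | 0.90/0.70 = 1.29 | 3.6 vs 2.8 |
| 50% | 9% vs 5% | 0.90/0.50 = 1.80 | 3.6 vs 2.0 |
| 30% | 9% vs 3% | 0.90/0.30 = 3.00 | 3.6 vs 1.2 |

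With equal true rates the ratio does not depend on p. At p = 5% or 20% it is the same, and the counts halve or double.

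If someone did test the difference, the chance of p < 0.05 from unequal detection alone would run from about 4% (p = 5%, 70% control detection) to about 38% (p = 20%, 30% control detection). This uses a normal approximation, which is rough at such counts.

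**Step 4: true harm gives the same data.** Suppose detection is 90% in both arms and the true rates are 10% and 0.05/0.90 = 5.6%. The observed rates are 0.10 × 0.90 = 9% and 0.056 × 0.90 = 5%, again a ratio of 1.80. The recorded counts cannot separate this case from the 50% row above.

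**Step 5: direction.** If under-recording fell on the intervention arm (50% against 90%), the ratio would be 0.05/0.09 = 0.56. Nothing in the article excludes either direction.

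**The case against.** **The observers may be blinded.** The article speaks of investigators, not of those delivering treatment, and has a trained blinded assessor. Under Frequency and plans for auditing trial conduct, the investigators train the nurses, so the two groups need not be the same people. A reader might infer that unblinded staff record the events and judge causality for their own procedure. The article does not say so. This part of the objection stands in full, but it leaves the unblinded self-reports untouched.

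**Controls are also observed.** Enemas as needed, perineal cleaning and skin protection in incontinent patients, the diary and on-site observations all give chances to notice anal problems. That narrows the gap. However, enemas and perineal cleaning are conditional and belong to the standard care of both arms, and the diary and observations appear as retention measures with no stated adverse event content. None of them matches planned digital contact. Equally, DRS is described as stimulation, so calling it an examination goes beyond the text.

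**Pre-existing lesions.** A reader might infer that fissures or bleeding present before enrolment go unrecorded and are logged as new events in the intervention arm only. The questionnaire sentence, "Participants will complete a well-designed questionnaire that encompasses age, sex, height, weight, types of strokes, and medication usage", does not mention them. But the full data collection plan is in Table 1, which is not shown. The Wexner constipation scale also contains a pain item, and a history of anorectal trauma or surgery is an exclusion. The gap cannot be shown.

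**No between-arm harm test is planned, and detail may sit elsewhere.** Both are fair. Adverse events are not a listed outcome, Statistical analyses names no test for them, and forms and observer roles are commonly left to a full protocol. The point therefore concerns a descriptive comparison and the collection method that the article does state.

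**Conclusion.** The point holds as a risk of detection bias, not as demonstrated bias. The article fixes self-report plus investigator observation as the method and does not state that ascertainment is blinded or equal. Participants and those delivering the intervention know the allocation, and planned contact with the affected sites differs by arm. For a trial that names safety as an aim, that leaves the comparison of anal bleeding, anal fissure and abdominal pain hard to interpret.

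The tempting stronger conclusion is that these events will be over-recorded under intervention and that the harm comparison is biased upward. The document does not support it: the observers' blinding is unstated, controls also have some contact, and the net direction is open. The ratios of 1.29 to 3.00 rest wholly on assumed detection probabilities and show only what unequal detection could do. An excess under intervention could also be real harm from DRS. I would class this as a cheap improvement.

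**What to change.** - In both arms, at baseline and at the existing week 2, 6 and 12 visits, use one identical short checklist: abdominal pain, anal bleeding, anal fissure, other.
- Have it completed in writing, or asked only after the Wexner and other outcomes have been scored, so that a conversation about anal events does not unblind the assessor before the primary outcome is recorded.
- Make checklist events that are new or worse than baseline the main between-arm safety comparison.
- Still report all events by arm, flagging those detected at DRS or massage sessions. Procedure-related harm seen only at sessions then stays visible. Reporting to the data monitoring committee continues as planned.
- State who collects and grades events and whether they know the allocation.

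**Cost.** A few added questions, with no new visit or examination. There is a residual risk of disclosing allocation to the assessor, and the answers still come from unblinded participants. A report of fissure may still depend on whether someone looked. The checklist stops at week 12, so the rest of the stated 12-month adverse event follow-up would rest on the existing method.
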